### Anesthetic managements

3.3

To avoid aortic rupture, systolic blood pressure will be controlled between 100 and 120 mm Hg with oral β-blockers and intravenous infusion of vasodilators (nitroprusside, etc.) before surgery. On surgery day, morphine hydrochloride 10 mg will be injected intramuscularly 1 hour before entering operation room. After entering the operating room, patients will be monitored with a 5-lead electrocardiography, pulse oximetry (SpO_2_), bispectral index (BIS), and invasive blood pressure through a left radial artery catheter. After tracheal intubation, a right internal jugular central venous catheter will be placed for monitoring of central venous pressure.

Anesthesia will be induced with intravenous midazolam, etomidate, sufentanil, and neuromuscular blockade drugs. After tracheal intubation, general anesthesia will be maintained with intravenous sufentanil, propofol, and either isoflurane or sevoflurane. BIS will be maintained at between 45 and 55 throughout surgery. The patient’ lungs will be mechanically ventilated with a FiO_2_ 100% oxygen and a 5-cmH_2_O positive end-expiratory pressure (PEEP). The end-tidal carbon dioxide pressure will be maintained at between 35 and 45 mm Hg by adjusting tidal volume of 6 to 8 mL/kg and respiratory rate of 10 to 15 times/min. During the cardiopulmonary bypass (CPB), mechanical ventilation will be discontinued and pulmonary static inflation (5 cmH_2_O) will be performed with compressed air.

### Surgical procedure^[10,11]^

3.4

Patients undergo median sternotomy and CPB. Cannulation of the femoral artery and/or right axillary artery will be performed for CPB. Furthermore, the right axillary artery cannulation will also be carried out for selective cerebral perfusion. After CPB is established and cooling is initiated, the ascending aorta will be clamped and cardiac arrest will be accomplished with cold cardioplegic solution during the cooling phase. When the nasopharyngeal temperature is decreased to 20 °C to 25 °C, circulatory arrest will be instituted. A stent graft and a 4-branch prosthetic graft will be used for arch replacement. After the open distal anastomosis is completed, the 4-branch prosthetic graft will be cross-clamped. Then the blood perfusion of the lower body will be started via the perfusion limb of the 4-branch prosthetic graft. Selective cerebral perfusion will be continued until the anastomosis to the left common carotid artery, innominate artery, and left subclavian artery is accomplished. Then CPB will be resumed to normal flow, and rewarming will be started. Valve-sparing root resection (aortic valve plasty, the David procedure, or valsalva sinus plasty) or valve graft replacement will be performed according to the subtype of the aortic root.

### Definitions

3.5

In all patients, the diagnosis of AAD will be confirmed by history, chest radiography, transthoracic, and contrast-enhanced computed tomogrphy or magnetic resonance imaging. The dissection is considered as AAD if the time from the onset of the symptoms to surgery is 14 days or less. This study will only include the type-A AAD according to the Stanford classifications.^[1,2]^

The definition criteria of the ALI includes an acute hypoxemic respiratory insufficiency with bilateral pulmonary infiltrates, but is not caused by left atrial hypertension according to the left ventricular ejection fraction (LVEF). The ALI will be defined using Murray lung injury score (Murray LIS).^[12,13]^ Murray LIS consists of 4 distinct clinical parameters, including the bilateral infiltrates observed on chest radiograph, oxygenation index (PaO_2_/FiO_2_ ratio), lung compliance, and PEEP value. The severity of ALI was quantified as follows: no = the Murray LIS 0, mild to moderate = the Murray LIS 0.1 to 2.5, and acute respiratory distress syndrome = the Murray LIS > 2.5. The Murray LIS will be calculated using a specially designed tool on the web site (http://med.39.net/tools/murray.html).

Hypertension is defined as systolic blood pressure ≥140 mm Hg and/or diastolic blood pressure ≥90 mm Hg, or the need of antihypertensive agents.^[14]^ Diabetes mellitus is defined as fasting glucose level ≥126 mg/dL (7.0 mmol/L), or a glycosylated hemoglobin (Hb) ≥6.5%,^[15]^ or treatment with oral hypoglycemic agents or insulin. Smoking status will be defined as current smokers according to self-report. A glomerular filtration rate less than 60 mL/min/1.73 m^2^, and increase in serum creatinine by more than 50% times baseline is defined as impaired renal function.^[16]^

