## Background

1

Patients presenting with aortic dissection within 2 weeks of the onset of symptoms are considered to have acute aortic dissection (AAD).^[1]^ AAD is a severe cardiovascular disease demonstrating the characteristics of acute onset and rapid development, with high morbidity and mortality. It has been shown that mortality of patients with AAD per hour early after the onset of symptoms is about 1% to 2%. Furthermore, mortality of patients with AAD who do not receive surgery is 58.0% in contrast to 26% in surgically treated patients.^[2,3]^ In patients with AAD, multiple organ failure including acute lung injury (ALI) is frequent.^[4,5]^ It is reported that 51% of patients meet the criterion of oxygenation impairment (oxygen fraction [PaO_2_/FiO_2_] ≤ 200 mm Hg) within 24 hour after onset of distal type AAD.^[6]^ Actually, preoperative ALI has been shown as a frequent complication associated with a number of untoward consequences, such as prolonged ventilator support, longer stay in intensive care unit and hospital, and even induces death. The previous work by Wang et al^[7]^ showed that the incidence of postoperative hypoxemia was up to 49.5% in Chinese adult patients undergoing Stanford type-A AAD surgery and postoperative hypoxemia was attributable to preoperative disturbance in oxygenation (78.5%, PaO_2_/FiO_2_ ≤ 200 mm Hg). In addition, preoperative hypoxemia can also result in surgery delay, which increases the risk of aortic rupture, cardiac tamponade, or even death. Therefore, the prophylaxis and/or treatment of preoperative ALI induced by AAD is important for final outcomes of patients.

Better understanding of the pathophysiology of preoperative ALI in the patients with AAD can improve clinical prophylaxis and/or treatment, but its underlying molecular and cellular mechanisms remain largely unknown. It is reported that the occurrence of oxygenation impairment on hospital days 2.5 in patients with Standford type-B AAD can be predicted by a multivariate logistic regression model.^[8]^ To our best knowledge, however, there is no study having assessed whether the preoperative ALI in Chinese adult patients undergoing the Standford type-A AAD surgery can be predicted by preoperative clinical and basic assessments. Thus, we put forward a prospective study strategy aiming to address the above issues.

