#### Murray lung injury score assessment

4.2.5

After routinely anesthesia and tracheal intubation, based on a FiO_2_ of 100%, a PEEP of 5 cmH_2_O, a tidal volume of 8 mL/kg, a 1:2 of inspiratory/expiratory ratio, and a respiratory rate of 10 per minute, the Murray LIS is obtained by radiographic findings on admission, oxygenation index (a PaO_2_/fraction of FiO_2_ ratio), lung compliance, and PEEP value.^[12,13]^

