## Statistical analysis

5

The data obtained in this study will be analyzed using SPSS 18.0 (SPSS Inc., Chicago, IL). Univariate and multiple logistic regression analyses will be used to determine the independent predictors of preoperative ALI. Univariate analysis will be applied for demographic data (age, sex, and BMI), comorbidities (smoking history, hypertension, and diabetes), preoperative data (hemodynamics, onset of symptoms to surgery, aortic diameter, LVEF, LVEDd, and EuroSCORE), surgical data (surgery time, hypothermic circulatory arrest time, intravenous colloid, crystalloid, and transfusion volumes), postoperative variables (intravenous colloid, crystalloid and transfusion volumes, urine volume, seroma volume of drainage, mechanical ventilation time, and in-hospital mortality), and serum measurements before surgery (coagulation/fibrinolysis, inflammatory, ROS, platelet, and endothelial cell function). In univariate analysis, variables associated with preoperative ALI with a *P* value <0.10 will be selected. Then, these selected variables will be put into the multiple logistic regression analysis to identify the independent predictors of preoperative ALI.

Receiver operating characteristic curve will be used to test discrimination of multivariate regression model and to determine the cutoff value in predicting preoperative ALI with sensitivity and specificity, respectively. The missing values will be displaced by means according to Intention-To-Treat rules. A *P* value <0.05 will be considered statistically significant.

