## Discussion

6

Population-based studies suggest an incidence of AAD of about 3 cases per 100,000 people per year in the United States of America.^[1]^ According to this incidence, there are almost 400,000 cases per year in China, which indicates over 20,000 patients with preoperative ALI per year. However, there has been no reliable incidence of preoperative ALI of such patients in China. Our study will be conducted in one of the largest clinic center of cardiovascular diseases in China, and a large nationally representative sample of the Standford type-A AAD in China will be collected. Therefore, the outcome of this trial can present the clinical characteristics of preoperative ALI in Chinese adult patients undergoing the Standford type-A AAD surgery.

In patients with AAD, ALI is a usual complication associated with untoward consequences or even leads to losing the chance of surgery. Although the risk factors and mechanisms of ALI are still unclear, the available evidence shows that systemic inflammatory response is activated through AAD surgery.^[4,17]^ Inflammation is a protective response essential for maintaining human health and fighting disease, but excessive inflammatory response can promote the irreversible cellular damage. The extensive activation of leckocyte and uncontrolled release of proinflammatory cytokines can increase the permeability of the vessel wall and thrombosis, which will contribute to the organs damage. Since the pulmonary vascular bed is an important reservoir of neutrophils, the lungs tend to be a major site of tissue damage by AAD.

Recent works have shown that coagulation/fibrinolysis and inflammation are host defense mechanisms, mutually dependent in mounting an adequate immune response against potentially injurious challenges.^[18]^ Furthermore, secondary fibrinolysis can aggravate ALI.^[19,20]^ Thus, we hypothesize that both the inflammation and coagulation are involved in ALI by AAD. By the statistical adjustment and analysis, it can be anticipated that findings of this study may reveal the related mechanisms of ALI by AAD. If these hypotheses are confirmed in our further clinical study, the treatments aimed to the pathophysiology of preoperative ALI can be recommended to decrease perioperative morbidity and mortality by ALI in patients with AAD. Thus, our findings have potentially clinical implications.

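### Study entry and a candidate predictor both use onset-to-surgery time, which the protocol says the outcome can lengthen, so reverse causation and some selection bias are possible

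*Protocol article*

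**What the plan says.** The protocol article dates acute aortic dissection in two ways. In the Background the clock stops when the patient presents: "Patients presenting with aortic dissection within 2 weeks of the onset of symptoms are considered to have acute aortic dissection". In section 3.5 it stops at the operation: "The dissection is considered as AAD if the time from the onset of the symptoms to surgery is 14 days or less". Section 3.5 goes on to restrict the study to acute type-A dissection, so its clock works as an entry rule.

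The protocol also describes how lung injury affects time to surgery. The Background says that "preoperative hypoxemia can also result in surgery delay", and the Discussion says that "ALI is a usual complication associated with untoward consequences or even leads to losing the chance of surgery".

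Section 5 includes the onset-to-surgery interval among the candidate predictors of preoperative ALI: "preoperative data (hemodynamics, onset of symptoms to surgery, aortic diameter, LVEF, LVEDd, and EuroSCORE". The entry rule for the multiple model is that "variables associated with preoperative ALI with a *P* value <0.10 will be selected". Section 2 states that the aims are incidence, independent risk factors and possible mechanisms, which goes beyond prediction.

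**The concern.** The interval from onset to surgery has two parts. The part before admission precedes the hospital course. The part from admission to surgery is the one that, on the protocol's own account, hypoxaemia can prolong. The planned variable merges them. If patients with ALI wait longer because of their ALI, a longer interval will be associated with ALI even if waiting does no harm, and the analysis cannot tell the two directions apart. A consequence of ALI could then be put forward as an independent risk factor.

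The entry rule raises a lesser issue. A patient who presents on day 12 and is operated on on day 15 has acute dissection under the Background wording but not under section 3.5. If the delay came from lung injury, the 14-day cut removes ALI patients preferentially, and the observed incidence would be somewhat low relative to patients who present within 14 days.

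**Working it through.** **Inputs from the protocol.** N = 130 and assumed ALI incidence 79% (section 3.2); screen at P<0.10 and significance at P<0.05 (section 5). Expected split: 130 × 0.79 = 102.7, so about 103 patients with ALI and 27 without.

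**Not in the protocol.** It gives no distribution of time to surgery and no size of delay due to ALI. There is therefore no figure of the plan's own to reproduce on this point, and everything below on delay is an assumption shown as a range.

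**Predictor.** Suppose ALI shifts the interval (on a suitable scale) by d within-group SDs and time has no effect on ALI.
- Expected test statistic: d × √(103 × 27 / 130) = 4.63 d.
- Chance of passing the screen: P(Z > 1.645 − 4.63 d). Chance of univariate P<0.05: P(Z > 1.96 − 4.63 d). The opposite tail adds at most 0.3 points.
- Non-causal odds ratio per SD, for normal groups of equal variance: exp(d).

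| d (assumed) | Odds ratio per SD | Passes P<0.10 | Reaches P<0.05 |
|---|---|---|---|
| 0 | 1.00 | 10% (two-sided) | 5% (two-sided) |
| 0.25 | 1.28 | 31% | 21% |
| 0.33 | 1.39 | 45% | 33% |
| 0.50 | 1.65 | 75% | 64% |

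A second model gives the same picture. Take log-normal times with SD of log time 0.8 to 1.0, let ALI multiply the time by 1.25 to 2.0, and ignore the 14-day cut. The odds ratio per SD is then 1.25 to 2.38, with 28% to 99% passing the screen and 18% to 98% reaching P<0.05.

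**Incidence.** Suppose the true incidence is 79%, 2% of non-ALI patients pass day 14, and a fraction a of ALI patients do. Observed incidence = 0.79(1 − a) / [0.79(1 − a) + 0.21 × 0.98].
- a = 5%: 0.7505 / 0.9563 = 78.5%, a loss of 0.5 points.
- a = 10%: 0.7110 / 0.9168 = 77.6%, a loss of 1.4 points.
- a = 25%: 0.5925 / 0.7983 = 74.2%, a loss of 4.8 points.

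For scale, the 95% half-width is 1.96 × √(0.79 × 0.21 / 130) = 7.0 points. In the log-normal model with median waits of 2 to 7 days, the observed incidence runs from 78.9% to 70.0%. The loss exceeds 7.0 points only with a median of 7 days and ALI doubling the wait. In those two settings half of the ALI patients would pass day 14. In every other setting the loss is at most 4.1 points.

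**Timing of the outcome.** Section 4.2.5 takes oxygenation and compliance after intubation, when the interval is complete. The film is earlier: "the Murray LIS is obtained by radiographic findings on admission, oxygenation index". The wait after admission cannot cause what that film shows, but the injury it shows may lengthen the wait.

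**The case against.** A reader might infer that both uses condition on the outcome. They do not. The entry rule selects on an interval that the outcome may lengthen, which is weaker than selecting on the outcome itself. Using that interval as a predictor is a question of reverse causation, which is a different problem.

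A reader might also infer that the reported incidence will be biased downward by a material amount. The documents do not support that. The target is patients undergoing surgery, and ALI is scored only once they are intubated. Someone operated on after day 14 is outside the population as section 3.5 defines it, so the loss is partly a limit on generalisability. The Background says only that hypoxaemia can delay surgery. A scenario such as a quarter of ALI patients waiting beyond two weeks has no source in the text.

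The strongest defence concerns the predictor. Most of the score is measured after the interval ends, so longer time since onset may truly affect lung injury. Plasma markers are drawn immediately after intubation (section 4.5), so time since onset may also confound the marker associations that serve the mechanistic aim. Dropping waiting time altogether would leave that unadjusted. In addition, passing a univariate screen is not the same as being reported as an independent predictor, because the multiple model follows.

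Most of this stands, and it shapes the fix. It does not remove the core problem: the merged variable cannot separate an effect of time on ALI from an effect of ALI on time, and the stated aims require that separation.

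**Conclusion.** The point holds in a limited form. Section 3.5 and section 5 both rely on an interval that the protocol itself says preoperative hypoxaemia can lengthen, and the Background and section 3.5 stop the 14-day clock at different events.

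The predictor is the part that matters, since reverse causation there needs nobody to cross day 14. The pass rates in the table rest on assumed shifts of 0.25 to 0.5 SD, no causal effect of time, and univariate tests. What the multiple model would show cannot be computed from the documents. Selection bias in the incidence is possible but probably small, and it cannot be quantified without the distribution of times.

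This is worth correcting because it alters what can be said about time as a risk factor. It does not show that the planned analysis will give a false result.

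**What to change.** 1. Reconcile the Background and section 3.5 so that one study-entry clock is used, preferably one that the outcome cannot lengthen: onset to presentation. This concerns who is counted in the study, not when anyone is operated on.
2. In section 5, split the interval. Use onset-to-admission time as the candidate risk factor.
3. Report admission-to-surgery time descriptively and do not interpret it as a cause of ALI. Use it only in a sensitivity analysis that adjusts the marker associations for time since onset.
4. Report how many patients were delayed past day 14 and how many were never operated on. The latter have no lung injury score under either clock, so they can only be counted.

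Cost: section 4.2.1 already records symptom onset, but the protocol does not list admission date and time, so these must be taken from the hospital record. The primary model will not include in-hospital waiting time, and under a presentation clock a few patients operated on after day 14 may enter the study.

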### Participants (inclusion and exclusion criteria)

3.2

The sample of subjects is estimated to 130 patients, based on a 79% incidence of ALI before surgery in patients with Stanford type-A AAD^[7]^ and the set power to 80% for a type I error of 5% (Power Analysis and Sample Size, PASS V11.0, NCSS, LLC. Kaysville, UT). A convenient sample will be recruited from the Beijing Anzhen Hospital. The AAD surgery in the Beijing Anzhen Hospital is performed in approximately 300 cases per year. If 30% of these patients are eligible and consent, we will meet our recruitment target in about 1.5 years, which can avoid the bias from the different levels of surgical procedures in different periods.

Patients aged 18 to 75 years will be included. The patients with coronary heart disease; heart failure; severe cardiac tamponade; unstable hemodynamics; nervous system abnormalities; clinically apparent malperfusion^[9]^ including lower limb, cerebral, coronary, and renal malperfusion; and visceral ischemia will be excluded. All patients enrolled in this study have normal hepatic and renal function according to the preoperative physical and laboratory examinations. No patient is prescribed with nonsteroidal anti-inflammatory drugs or corticosteroids before or after admission. All patients will be informed and consented with regard to their participation in the study.

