#### Echocardiogram

4.2.3

The data of preoperative echocardiogram will be recorded, including aortic diameter, LVEF, and left ventricular end-diastolic dimension (LVEDd).

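### Left atrial hypertension is ruled out by LVEF alone, with no cut-off, so hydrostatic lung oedema with preserved LVEF can be counted as ALI

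*Protocol article*

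**What the plan says.** Section 3.5 describes ALI as acute hypoxaemic respiratory insufficiency with bilateral infiltrates that "is not caused by left atrial hypertension according to the left ventricular ejection fraction (LVEF"). It states no LVEF threshold and no other evidence for this exclusion.

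The same section then scores ALI with the Murray lung injury score, built from four items, "including the bilateral infiltrates observed on chest radiograph, oxygenation index (PaO_2_/FiO_2_ ratio), lung compliance, and PEEP value". Severity is graded "no = the Murray LIS 0, mild to moderate = the Murray LIS 0.1 to 2.5", so only a score of zero is labelled as no ALI.

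Other sections that bear on the point:
- **4.2.3** lists the preoperative echocardiographic data, "including aortic diameter, LVEF, and left ventricular end-diastolic dimension (LVEDd").
- **3.3** names one filling pressure: "a right internal jugular central venous catheter will be placed for monitoring of central venous pressure".
- **3.2** sets the exclusions, beginning "The patients with coronary heart disease; heart failure; severe cardiac tamponade; unstable hemodynamics; nervous system abnormalities". Heart failure is not defined, and aortic regurgitation is not named.
- **3.4** foresees root and valve surgery: "Valve-sparing root resection (aortic valve plasty, the David procedure, or valsalva sinus plasty) or valve graft replacement will be performed", according to the root subtype.
- **Section 4** plans a second review of all ALI cases, and of a random sample of non-ALI cases, by an independent expert blinded to the first adjudication.

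**The concern.** The definition sets a condition, no left atrial hypertension, and ties it to a measure that cannot test it. Ejection fraction describes how well the ventricle empties. Left-sided filling pressure can be raised while ejection fraction is normal, and a leaking aortic valve is one way this can happen. Hypoxaemia and infiltrates from that cause would pass the LVEF check.

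This matters because one outcome serves both main aims in section 2: the incidence of preoperative ALI and its independent predictors. False cases raise the incidence. They also take patients out of a small comparison group and mix two mechanisms among the cases, while the study wants to learn about inflammation and coagulation in lung injury.

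**Working it through.** **1. Does anything else in the document test left atrial pressure?** The protocol states no figure on this point to reproduce, so the first step is to compare the sections.
- The Murray items (3.5) describe the lung and the ventilator setting. None is a cardiac item. Oedema can worsen infiltrates, oxygenation and compliance just as lung injury can.
- Of the listed echocardiographic items (4.2.3), none is a filling-pressure sign or a regurgitation grade.
- Central venous pressure (3.3) is a right-sided measure, taken after intubation.
- The grading in 3.5 sets the bar for a case low: as written, any score above 0 is at least mild to moderate ALI.

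Nothing stated fills the gap that LVEF leaves.

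**2. How large could the effect be?** The documents give no rate, so the first two inputs are assumptions.
- Share with moderate or worse regurgitation: 20% to 40% (assumed).
- Share of those with raised filling pressure and a lung picture that would count: 10% to 30% (assumed).
- Sample size 130 and planning incidence 79% (section 3.2).

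Share affected, a: 0.20 × 0.10 = 0.02 to 0.40 × 0.30 = 0.12. In patients: 130 × 0.02 = 2.6 to 130 × 0.12 = 15.6.

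*Oedema independent of true ALI.* Only affected patients without true ALI become false cases, so the rise in incidence is a × (1 − 0.79):
- 0.02 × 0.21 = 0.0042, or 0.4 points (130 × 0.0042 = 0.5 patients)
- 0.12 × 0.21 = 0.0252, or 2.5 points (130 × 0.0252 = 3.3 patients)

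*No affected patient has true ALI.* Every affected patient is a false case, so the rise is a itself: 2 to 12 points, or about 3 to 16 patients.

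*Dependence on the 79%.* If true incidence were 50%, the independent case would give 0.02 × 0.50 = 1 point to 0.12 × 0.50 = 6 points.

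**3. Against sampling error.** The 95% half-width at 79% with 130 patients is 1.96 × √(0.79 × 0.21 / 130) = 0.070, or 7.0 points. At 79%, the independent case lies well inside this. Only the upper part of the extreme case exceeds it.

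**4. Against the comparison group.** Expected non-ALI patients: 130 × 0.21 = 27.3. Those lost to false cases are 2% to 12% of this group in the independent case. In the extreme case they are 2.6 / 27.3 = 10% to 15.6 / 27.3 = 57%. The predictor analysis therefore has less room for such errors than the incidence estimate.

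**The case against.** The strongest reply is that the plan has other safeguards. Section 3.2 excludes heart failure, unstable haemodynamics, severe tamponade and coronary disease, and does not tie heart failure to LVEF. A patient with hypoxaemia and bilateral infiltrates from high left-sided pressure looks clinically like heart failure, so many such patients should never enter. Section 4 adds a blinded expert review of every ALI case, which is the right place to catch false positives. Both points stand as reductions of the problem. Neither closes it: heart failure is undefined, a score just above 0 suffices for a case, and no criterion other than that of 3.5 is stated for the reviewer.

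It is also fair to say that aortic regurgitation appears nowhere in the document. It is inferred from the procedures in 3.4, which are chosen by root subtype. They show that valve and root disease is expected, not how often regurgitation raises filling pressure with a normal LVEF.

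The list in 4.2.3 need not be exhaustive, and an article may leave form fields to the full protocol. The absence of a regurgitation grade is therefore not a fault in itself. What remains is the rule as stated in 3.5.

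Finally, a reader might infer that left ventricular end-diastolic dimension, a candidate in section 5, will emerge as a spurious predictor, or that marker effects will be diluted. Both are possible, but no figure in the document supports either. Nor does it show that chamber enlargement would arise within the 14-day limit of 3.5.

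**Conclusion.** The point holds as a weakness in the stated outcome definition. LVEF alone, without a cut-off, cannot establish that left atrial hypertension is absent, and no other stated measurement does so. Hydrostatic oedema with preserved LVEF can therefore be counted as ALI.

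A reader might go further and conclude that oedema from aortic regurgitation is routinely counted as ALI and that the incidence will be seriously inflated. The documents do not support that. They give no frequency, and the exclusions and second review will remove some of these patients. The 2% to 12% share is an assumption and is not adjusted for those exclusions. Under it, the inflation at 79% is about 0.4 to 2.5 points with independence and 2 to 12 points in the extreme case. The true size is unknown. The change is worth making because it is cheap and because the outcome feeds both main aims.

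**What to change.** - **Section 3.5:** base the judgement on left atrial hypertension on the available echocardiographic and clinical evidence rather than LVEF alone, and say how it relates to the heart failure exclusion in 3.2.
- **Section 4:** state that the second reviewer applies the same criterion.
- **Section 4.2.3:** record aortic regurgitation grade and, where reported, left atrial size from the preoperative echocardiogram already planned.
- **Section 5:** report incidence and the predictor model with and without patients who have moderate or worse regurgitation or judged raised filling pressure. In this sensitivity analysis, exclude them. Moving them to the non-ALI group would put hypoxaemic patients with infiltrates among the comparators.

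Do not add regurgitation grade as a further covariate. With about 27 non-ALI patients expected and a long candidate list already in section 5, the model cannot carry it.

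The cost is a few form fields, some missing echocardiographic data, and a somewhat smaller sample in the sensitivity analysis. Treatment, recruitment and sample size do not change.

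### The protocol defines ALI in two ways that disagree, one of which counts any Murray score above 0 as ALI, and its 79% planning rate appears to rest on yet another criterion

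*Protocol article*

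**What the plan says.** - **Clinical criteria (section 3.5, Definitions).** ALI is "an acute hypoxemic respiratory insufficiency with bilateral pulmonary infiltrates, but is not caused by left atrial hypertension", the last point being judged from LVEF. No numeric PaO2/FiO2 threshold is attached to the hypoxaemia.
- **Murray rule (same paragraph).** The next sentence reads "The ALI will be defined using Murray lung injury score (Murray LIS". The grading that follows is "no = the Murray LIS 0, mild to moderate = the Murray LIS 0.1 to 2.5", with acute respiratory distress syndrome above 2.5.
- **Components (section 3.5).** "Murray LIS consists of 4 distinct clinical parameters, including the bilateral infiltrates observed on chest radiograph"; the other three are PaO2/FiO2, compliance and PEEP. The score comes from a web tool, and the article does not show how each component is scored.
- **Measurement (section 4.2.5).** After intubation all patients are scored at FiO2 100% and PEEP 5 cmH2O, but "the Murray LIS is obtained by radiographic findings on admission".
- **Planning rate (section 3.2).** The 130 patients are based on a 79% preoperative ALI incidence. The Background reports the same cited source as "postoperative hypoxemia was attributable to preoperative disturbance in oxygenation (78.5%, PaO_2_/FiO_2_ ≤ 200 mm Hg".
- **Use of the outcome.** Section 4 has a blinded expert re-review all ALI cases and a sample of the others. Section 5 models ALI by univariate and multiple logistic regression and draws an ROC curve. Neither section says which definition applies.

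**The concern.** ALI is the first aim (its incidence), the label that is re-adjudicated, and the dependent variable of every regression and of the ROC analysis. If two rules in one paragraph sort the same patients differently, both main results depend on a choice that the protocol leaves open and that could be made after the data are seen.

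The Murray rule adds a second problem. When ALI is the common state, the non-ALI patients limit the information in the logistic model. A cut-off at any score above 0 is the widest possible reading of the scale, so it makes that group as small as it can be.

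**Working it through.** **1. The plan's own figure.** The 79% incidence, 80% power and 5% type I error do not determine N, because no null value, effect size or precision is given. One unstated quantity that reproduces 130 is a 95% confidence half-width of 7 points: 1.96² × 0.79 × 0.21 / 0.07² = 130.06. Power does not enter that formula. A two-sided one-sample test against 68% gives 131, also close. So N cannot show which definition was intended.

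**2. The criteria side by side.** Assume that bilateral infiltrates, and a PaO2/FiO2 of 200 or less, each score above 0.

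| Patient | Clinical criteria | LIS above 0 | PaO2/FiO2 ≤200 alone |
|---|---|---|---|
| Reduced compliance only | no ALI | ALI | no ALI |
| PaO2/FiO2 ≤200, no infiltrates | no ALI | ALI | ALI |
| PaO2/FiO2 ≤200 and infiltrates, from left atrial hypertension | no ALI | ALI | ALI |
| PaO2/FiO2 ≤200 and infiltrates, not cardiac | ALI | ALI | ALI |

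Everyone who is ALI under either of the other criteria also has LIS above 0, but the reverse fails. Incidence under LIS above 0 is therefore at least as high as under each of them.

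**3. Expected comparators.** Inputs: N = 130 and 79% (section 3.2). Let q be the share of patients with PaO2/FiO2 above 200 who have another non-zero component. The documents do not give q, so the values below are assumptions.

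Incidence under LIS above 0 = 1 − (1 − 0.79)(1 − q); expected non-ALI = 130 × 0.21 × (1 − q).

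| q | Incidence | Non-ALI of 130 |
|---|---|---|
| 0 | 79.0% | 27.3 |
| 0.25 | 84.3% | 20.5 |
| 0.50 | 89.5% | about 14 |
| 0.75 | 94.8% | 6.8 |

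At q = 0 the binomial 95% range is 19 to 37. Using 78.5% instead of 79% gives 130 × 0.215 = 28.0.

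**4. What fewer comparators cost.** For one continuous predictor, with two-sided 5% and 80% power, the detectable odds ratio per SD is exp[(1.96 + 0.84) / √(130 × p × (1 − p))]. This gives 1.83 at p = 79%, 2.27 at 90% and 3.09 at 95%. Sections 4.5 and 5 list about 49 candidate variables (24 clinical, 25 laboratory), so even 27.3 comparators is 27.3 / 49 = 0.56 per candidate.

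**5. PEEP.** It is the same for everyone, so its component cannot separate patients. If the tool scores 5 cmH2O as 0, nothing is added. If it scores it above 0, every patient has LIS above 0 and no comparator is left. The article does not show which.

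**6. Timing.** The radiograph component dates from admission; oxygenation, compliance and PEEP date from after intubation. Infiltrates that appear in between are not scored. This error lowers the LIS, so it runs against the inflation in step 3.

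**The case against.** The strongest defence is that the two statements work in sequence: the clinical criteria identify ALI, and the LIS only grades its severity. The grading sentence does speak of severity, and section 4 refers to an initial ALI adjudication. But the text says that the LIS defines ALI, and the scale has a no-ALI category at 0, which a patient already selected for infiltrates and hypoxaemia should not occupy. Section 4 does not say what the adjudication is judged against. If grading was meant, the wording still has to change.

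Several stronger readings are tempting, and the documents do not support them:

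- **Three outcome definitions.** A reader might infer this. The PaO2/FiO2 criterion belongs to a cited study and enters only as a planning input. The Background sentence can also be read as the share of postoperative hypoxaemia attributable to preoperative hypoxaemia, in which case 79% may not be an incidence at all.
- **Almost no comparators.** This depends on q and on how PEEP is scored, and neither is given. At the protocol's own rate about 27 remain.
- **A ceiling of 78.5% under the clinical criteria.** This would need the 200 threshold, which section 3.5 does not set. A looser threshold could give a higher rate.
- **A 14-day gap inside one score.** The 14 days run from symptom onset to surgery. The interval from film to intubation is not stated.

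Two further points stand in part. Fixed ventilator settings make oxygenation and compliance comparable between patients, so a constant PEEP is not in itself an error; it matters only for a cut-off at 0. Section 3.2 already excludes heart failure and coronary disease, which covers some of what the left atrial hypertension criterion would remove.

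**Conclusion.** The concern holds. Section 3.5 contains two rules for ALI that disagree, nothing in the article reconciles them, and the planning rate appears to come from another criterion. This is a contradiction in the stated outcome, not a detail left to an analysis plan.

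The disagreement itself needs only the wording: a no-ALI category at exactly 0 means that one non-zero component suffices, whereas the clinical criteria require several findings together. The upper figure of about 27 comparators needs two assumptions: that PaO2/FiO2 of 200 or less scores above 0, and that 79% is a real rate for that criterion. The figure of about 14 is an illustration at q = 0.5, not an estimate. The size of the inflation cannot be obtained from the documents.

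The point must be fixed before analysis, because both the incidence and every regression depend on it.

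**What to change.** Reconcile sections 3.2, 3.5, 4, 4.2.5 and 5:

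1. Name one binary ALI outcome and use it for incidence, adjudication, regression and ROC. It should not be LIS above 0 alone, since that contradicts the clinical criteria in the same section.
2. State how the clinical criteria and the LIS relate, and give the oxygenation threshold. Which threshold is the sponsor's choice.
3. Analyse the LIS as an ordinal or continuous secondary outcome, leaving out the constant PEEP component.
4. Restate the planning rate on the chosen definition, and recheck the expected number of non-ALI patients in 130.
5. Score the radiograph on the latest preoperative chest image where one exists; otherwise report the gap between film and scoring.

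The cost is mainly wording. The protocol does not guarantee a chest image later than admission, so item 5 relies on what is available, and recording the gap is a small addition. The reported incidence may be lower than under LIS above 0.
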